## INTRODUCTION

Tobacco use poses a significant public health threat in China, the world’s largest tobacco producer and consumer^1^. With over 1 million annual tobacco-related deaths, projected to reach 2 million by 2030, important action is needed^2^. The Healthy China 2030 initiative aims to reduce adult smoking rates from 27.7% in 2015 to 20% by 2030^3^, necessitating the implementation of evidence-based smoking cessation practices.

Brief verbal intervention for smoking cessation (BISC), a 1-3 minute verbal advice delivered by health professionals during routine consultations, is a highly effective^4^ and a cost-efficient approach^5^. Primary healthcare (PHC) providers are ideally positioned to deliver BISC^6,7^ due to their credibility^8,9^ and frequent contact with patients, particularly those with conditions like diabetes and hypertension, who could greatly benefit from smoking cessation^10^ and those who frequent PHC clinics.

Despite BISC’s effectiveness and an appropriate health workforce, its implementation in China has been insufficient^11,12^. Clinical data show that the percentage of clinicians who actively ask whether patients smoked is low, and only about one-third (33.9%) of patients report receiving such advice^13^. This demonstrates that BISC has not yet become a routine practice.

This challenge highlights a crucial gap in China’s research landscape, which has largely focused on developing new interventions rather than effectively implementing existing ones. To address this, our type 3 hybrid effectiveness-implementation trial will apply a rigorous and innovative methodology.

This study use of the Multiphase Optimization Strategy (MOST) framework to optimize a tobacco cessation implementation strategy, providing a novel paradigm for future public health research. The methodology and findings from this study are expected to be highly relevant and adaptable to other low- and middle-income countries (LMICs) facing similar public health challenges. The primary objective of this study is to identify the optimal set of implementation techniques for promoting BISC based on prior research on barriers and facilitators.

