**Figure 2 F0002:**
[figure not shown]
Sampling procedure of primary healthcare facilities with 640 clinicians, Guangdong Province, China, January 2026 – December 2026

In the second stage, all primary healthcare institutions under the jurisdiction of the recruited local health authorities in these three cities will be included in the sampling frame. These institutions will then be regrouped into PSUs based on the number of clinicians. This ensures that each unit has a sufficient number of clinicians, preventing the exclusion of smaller institutions from the sampling process. The PSUs will then be sampled using a probability proportional to size (PPS) sampling method.

The study will be conducted as a cluster-randomized trial. The intervention will be delivered to the entire cluster (PSU), but the intervention’s effect will be measured at the clinician level. The measurement is based on the average performance of a random sample of clinicians within the cluster. This is achieved through unannounced standardized patient (USP) visits, which function as the final step of the sampling process. A minimum of 80 USP visits will be assigned to each experimental condition.

*Sample size and power*

Power analyses were conducted to determine the sample size needed to test the effect of the implementation strategies on our primary outcome, ‘clinician advice to quit’. The detailed definition and measurement of this outcome are provided in the section on study outcomes. Based on prior research, the baseline rate for this outcome was 33.9%^13^. Through stakeholder consultation, it was determined that a 40% increase in delivery, resulting in a final primary outcome of 47.46%, would be considered a clinically meaningful effect. Assuming a two-tailed test with an alpha level of 0.05 and a desired power of 0.8, a sample size of 28 participants per cluster is required. Accounting for the cluster-randomized design with a design effect (Deff) of 2 and adjusting for an anticipated 20% loss to follow-up, the sample size has been intentionally increased to further enhance statistical power for detecting higher-order interactions. Consequently, the required sample size for one experimental condition is approximately 80 participants. Given our study design with eight conditions (one condition per PSU, for a total of eight PSUs), this translates to 640 participants in total.

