		Daily cigarette consumption		Number of cigarettes smoked daily. To assess a reduction in smoking behavior.	Quantitative data and qualitative data	-	Telephone callback			●	●	●
	Tertiary outcome	Patient satisfaction with the BISC provided by the clinician		The patient’s perceived satisfaction with how the physician implemented BISC during the consultation.	Quantitative data and qualitative data	-	Telephone callback			●	●	

a I: Enrolment. II: Baseline (i.e. before the first of BISC implementation). III: Mid-term (i.e. at the middle of BISC implementation), which will be executed the weeks 1, 3, 5, 7, 9 and 11 after the start of the BISC implementation. IV: Endline (i.e. at the end of BISC implementation). V: Follow-up (i.e. maintenance of the BISC), which will be executed 6 months after the endline.

b Data collection via telephone callbacks with patients in periods I and V; Data collection by USP visits in period IV. IOF: Implementation Outcomes Framework. BISC: brief intervention for smoking cessation. USP: unannounced standardized patient.

*Outcomes*

The study outcomes will be aligned with the principles of Proctor’s Implementation Outcomes Framework (IOF) and the RE-AIM framework. According to the type 3 hybrid design, the outcomes are categorized into primary and secondary aims to reflect the dual focus on implementation strategies and patient-level effects.

Primary aim: implementation outcomes

The primary aim of this study is to evaluate the effectiveness of the implementation strategies. These outcomes will be assessed by a combination of methods to ensure a comprehensive evaluation.

The primary outcomes, ‘clinician ask smoking status’ and ‘clinician advise to quit’, will be assessed using unannounced standardized patient (USP) visits. These outcomes serve as key measures of fidelity to the brief intervention protocol. The secondary outcomes, ‘clinician ask about number of cigarettes smoked’, ‘clinician discuss the harms and benefits of quitting’, and ‘clinician provide a referral’, will also be measured using a combination of USP visits for clinicians and telephone callbacks for outpatients.

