### Data analysis

*Quantitative analysis*

Data will undergo de-identification prior to analysis. Baseline characteristics of participants will be presented, utilizing mean and standard deviation for continuous variables and frequency and percentage for categorical variables. The trial outcome analysis will adhere to the intent-to-treat principle. Generalized estimating equations (GEE) with a binomial distribution and log link function will be used for the primary binary outcome, with clustering specified at the PSU level, to assess the main and interaction effects of the four implementation techniques on adherence to BISC practices among primary healthcare clinicians. The model will account for robust predictors of outcomes, including baseline adherence scores and sociodemographic factors of clinicians^24-26^. Effect coding will be applied to each experimental condition, and subgroup analyses based on age, gender, clinician level, and facility will be conducted to further explore the impact of different technique combinations on BISC implementation. Sensitivity analyses, involving imputation of missing values through random forest, will be performed to validate the robustness of the findings^27^. For continuous outcomes, GEE models with a Gaussian distribution and identity link function will be employed, adjusting for the same covariates and clustering at the PSU level. In the analysis, control for covariates including clinician-related information (gender, age, professional title, and department) and patient-related information (gender, age, primary diagnosis, and smoking status). We will perform subgroup analyses on patient smoking status, level of tobacco dependence, and clinician department to investigate differences in BISC implementation among different types of clinicians for various types of patients.

Hypothesis tests will be two-sided, with statistical significance set at p<0.05. All statistical analyses will be performed using Stata version 16.0 and R version 4.5.2.

*Qualitative analysis*

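### Table 2 footnote b names no data source for the baseline and mid-term fidelity outcomes, and the 33.9% planning rate is patient-reported while the primary outcome is USP-observed

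*Protocol article*

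**What the plan says.** **Instrument and timing.** The Outcomes section has both primary outcomes (asking smoking status, advising to quit) assessed by USP visits. Strengths and limitations describes those visits as a measurement at one time point. Table 2 lists USP visit or telephone callback as the acquisition method for both outcomes and marks them in periods II (baseline), III (mid-term, six rounds from week 1 to week 11), IV (endline) and V (six months later). Period I (enrolment) is not marked. Footnote b assigns the sources: "Data collection via telephone callbacks with patients in periods I and V; Data collection by USP visits in period IV".

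**Use of baseline.** Data analysis states: "The model will account for robust predictors of outcomes, including baseline adherence scores and sociodemographic factors of clinicians".

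**Planning rate.** Sample size and power states: "Based on prior research, the baseline rate for this outcome was 33.9" per cent. The Introduction, with the same citation, describes the figure this way: "only about one-third (33.9%) of patients report receiving such advice". The target follows: "it was determined that a 40% increase in delivery, resulting in a final primary outcome of 47.46" per cent.

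**The concern.** There are two separate problems.

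First, the footnote and the table columns cannot both be right. Read literally, the footnote provides callbacks in a period with no measurement and leaves baseline and six mid-term rounds unassigned. The gap reaches the primary analysis through the baseline covariate, whose source and level (clinician or primary sampling unit, PSU) are not stated. If baseline is by callback, the covariate is patient-reported and the outcome is USP-observed, and the text should say so.

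Second, the plan uses USPs because it regards them as more valid than self-report, yet it takes a self-reported rate, without qualification, as the rate of the USP outcome. Because the meaningful effect is a relative rise of 40%, the absolute difference to be detected moves with the control rate, and so does power.

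**Working it through.** **1. Table 2 against footnote b (primary outcomes)**

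| Period | Marked in Table 2 | Source in footnote b |
|---|---|---|
| I Enrolment | no | callback |
| II Baseline | yes | none |
| III Mid-term | yes | none |
| IV Endline | yes | USP |
| V Follow-up | yes | callback |

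Reading I as a slip for II would still leave III unassigned. The section on effectiveness outcomes does not fill the gap: it describes calls at the end of the intervention and at six months, to patients who received the brief intervention.

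**2. Level of the baseline covariate.** Sample size and power gives one PSU per condition and eight PSUs. A factorial model with all main and interaction effects has 1 + 3 + 3 + 1 = 8 coefficients for eight PSUs. A baseline proportion that is constant within a PSU is then an exact linear combination of the condition terms and cannot be estimated. Only a covariate that varies between clinicians within a PSU can be.

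**3. The plan's own figures.** Inputs: control rate 33.9%, relative rise 40%, design effect 2, loss 20%, 640 clinicians (all from Sample size and power), and "Assuming a two-tailed test with an alpha level of 0.05 and a desired power of 0.8".

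- Target: 0.339 × 1.40 = 0.4746, as stated.
- The plan then says: "a sample size of 28 participants per cluster is required". This does not follow from those rates. The usual two-proportion formula gives 205 per factor level (220 with continuity correction). A level pools four conditions, so that is 52 to 55 per condition before inflation.

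**4. Power for a main effect with 640.** Each level has 640/2 = 320. With a design effect of 2 the effective number is n = 160, and after 20% loss it is 128. For control rate p:

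Power = Φ( 0.4p / √{[p(1−p) + 1.4p(1−1.4p)]/n} − 1.96 )

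At p = 0.339 the variance sum is 0.2241 + 0.2494 = 0.4734.

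- n = 160: SE = √(0.4734/160) = 0.0544; 0.1356/0.0544 = 2.49; Φ(0.53) = 0.70.
- n = 128: SE = 0.0608; ratio 2.23; Φ(0.27) = 0.61.

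The documents give no USP-observed rate, so the other rows are assumptions:

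| Control rate | Target | Power, n = 160 | Power, n = 128 |
|---|---|---|---|
| 20% | 28% | 39% | 32% |
| 25% | 35% | 50% | 42% |
| 33.9% | 47.46% | 70% | 61% |
| 40% | 56% | 83% | 74% |
| 50% | 70% | 96% | 92% |

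**5. Detectable rate at 80% power from 33.9%.** Setting the ratio to 1.96 + 0.84 gives 49.1% for n = 160 and 50.9% for n = 128, relative rises of about 45% and 50% (0.491/0.339 and 0.509/0.339).

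**6. Reference distribution.** These figures use the normal. With eight PSUs there are four per factor level. A t reference on 6 degrees of freedom (an assumption) lowers the 33.9% row to about 55% and 47%.

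**The case against.** The strongest reply is that the intent can be worked out. Only two instruments are listed for these outcomes and USPs are used once, at endline. Patient sociodemographics are already collected by callback in II to V. By elimination II and III are callbacks, and the numeral I is a slip. This stands as the likely reading. A reader might infer from the footnote that no baseline measurement will exist; the documents do not support that. They do leave the source to be guessed, and nothing says that callbacks will be linked to individual clinicians.

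A reader might also infer that callback and USP records will be pooled, or compared before and after. No section plans this. Baseline adherence enters only as a covariate, and the randomised comparison at endline uses one instrument. An explicit statement is still worthwhile. Table 2 names both instruments for the primary outcomes. The covariate list also includes patient gender and smoking status, which cannot vary in USP data because all three USP cases are male current smokers. Those covariates may be meant only for patient-level outcomes, but the text does not say so.

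Finally, planning from a published patient-reported rate is an assumption, not an error, and its direction is unknown. A reader might infer that the USP rate must be lower and the trial therefore weaker. Nothing in the documents shows that: each USP case is a current smoker whose condition calls for the intervention, so the rate could as well be higher. This objection stands, and it is why the range runs on both sides of 33.9%.

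**Conclusion.** The concern holds in two limited parts. Footnote b contradicts Table 2 and has to be reconciled, because the primary model depends on a baseline measurement whose source and level are not fixed. The 33.9% is described as the rate of the primary outcome when it is a patient-reported figure for an outcome that USPs will record.

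The validity of the endline comparison is not in question. What is at stake is a usable baseline covariate and an honest power statement. Over assumed control rates of 20% to 50%, power runs from 39% to 96% (32% to 92% after loss). This assumes the 40% relative rise, equal factor levels of 320, a design effect of 2 and a normal reference, which is optimistic with four PSUs per level.

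The 70% (61%) at the plan's own 33.9% should not be charged to the instrument mismatch. It reflects the sample-size arithmetic and would remain if 33.9% were a USP rate.

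**What to change.** 1. Reconcile footnote b with the period columns, stating the source for II and III. Keep the endline callbacks that the Outcomes section describes for secondary fidelity outcomes and for confirming receipt of the intervention.
2. State that the primary outcomes are the USP records at period IV only, and that callback records are not analysed as the same outcome.
3. State the source and level of the baseline adherence covariate. It has to be linked to the clinician. If callbacks cannot be linked in this way, drop it from the primary model.
4. Label 33.9% as a patient-reported assumption. Restate power and detectable difference for 640 over a range on both sides of it, with a reference distribution suited to eight PSUs. Use the team's earlier USP visits for a planning rate only if they recorded advice to quit, which the article does not show.

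The cost is a corrected footnote, a few sentences in Outcomes, Data analysis and Sample size, and a short recalculation. The restated power may be less favourable than 80%. Linking callbacks to clinicians may need a small change in data collection, best settled before baseline data are used.

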### Study variables

*Demographic variables*

Demographic variables include institution information, clinician sociodemographics, and patient sociodemographics. Detailed variables, data collection methods, and time points are summarized in Table 2.

**Table 2 T0002:** Study variables of the type 3 hybrid effectiveness-implementation trial, Guangdong, China, January 2026 – December 2026

*Category*	*Outcome* *type*	*Variable*	*Theoretical basis*	*Definition*	*Variable type*	*Tool*	*Acquisition* *methods*	*Study periods ^a^*				
								*I*	*II*	*III*	*IV*	*V*
**Basic information**	Institution information	Institution location, level, etc.		-	-	-	Questionnaire survey	●				
	Socio-demographic of clinician	Gender, age, title, department, etc.		-	-	-	Questionnaire survey	●				
	Socio-demographic of patient	Gender, age, primary diagnosis, etc.					Telephone callback		●	●	●	●
**Implementation outcomes**	Primary outcome	Clinician asks smoking status	IOF: Fidelity RE-AIM: Implementation	From the first step in the BISC implementation steps in the China Clinical Cessation Guidelines (2015 edition), indicating whether the clinician asked smoking status or not.	Quantitative data, dichotomous variable (0,1)	Questionnaire	USP visit/telephone callback^b^		●	●	●	●
		Clinician advises to quit	IOF: Fidelity RE-AIM: Implementation	From the fourth step in the BISC implementation steps in the China Clinical Cessation Guidelines (2015 edition), indicating whether the clinician advised to quit.	Quantitative data, dichotomous variable (0,1)	Questionnaire	USP visit/telephone callback^b^		●	●	●	●
	Secondary outcome	Clinician asks about number of cigarettes smoked	IOF: Fidelity RE-AIM: Implementation	From the second step in the BISC implementation steps in the China Clinical Cessation Guidelines (2015 edition), indicating whether the clinician asked about number of cigarettes smoked.	Quantitative data, dichotomous variable (0,1)	Questionnaire	USP visit/telephone callback		●	●	●	●
		Clinician discusses the harms and benefits of quitting	IOF: Fidelity RE-AIM: Implementation	From the third step in the BISC implementation steps in the China Clinical Cessation Guidelines (2015 edition), indicating whether the clinician told about harms/benefits of quitting.	Quantitative data, dichotomous variable (0,1)	Questionnaire	USP visit/telephone callback^b^		●	●	●	●

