		Clinician provides a referral	IOF: Fidelity RE-AIM: Implementation	From the fifth step in the BISC implementation steps in the China Clinical Cessation Guidelines (2015 edition), indicating whether the clinician referral patient to smoking cessation clinic.	Quantitative data, dichotomous variable (0,1)	Questionnaire	USP visit/telephone callback^b^		●	●	●	●
		Coverage of BISC delivery	IOF: Penetration RE-AIM: Reach	Percentage of patients who received BISC as compared to the patients who attended to PHC.	Quantitative data, percent (0–100%)	Questionnaire	USP visit/telephone callback^b^		●	●	●	●
	Tertiary outcome	Applicability of BISC delivery	IOF: Feasibility	The extent to BISC can be successfully carried out within PHC clinician.	Quantitative data 0–100 points	NPT questionnaire	Questionnaire survey				●	
		Acceptance of BISC delivery	IOF: Acceptability REAIM: Adoption, Maintenance	The perception among the PHC facilities that BISC implementation techniques is agreeable, palatable, or satisfactory.	Qualitative data	Interview outline	Semi-structured interview				●	
			IOF: Adoption RE-AIM: Adoption	The intention, initial decision, or action to try or employ BISC from the perspective of the PHC facilities.							●	
			IOF: Appropriateness RE-AIM: Adoption	The perceived fit, relevance, or compatibility of BISC for the PHC facilities; and/or perceived fit of BISC to address a particular issue or problem.							●	
		Sustainability of BISC delivery	IOF: Sustainability RE-AIM: Adoption, Maintenance	The possibility to BISC is maintained or institutionalized within PHC clinician’s ongoing, stable operations.	Quantitative data	The Program Sustainability Assessment Tool (PSAT)	Questionnaire survey				●	
		Sustainment of BISC delivery	IOF: Sustainability; RE-AIM: Maintenance	The continued implementation of BISC by the primary care clinician over time.	Quantitative data and qualitative data	The Provider Report of Sustainment Scale (PRESS) and interview outline	Questionnaire survey and semi-structured interview					●
		Cost of BISC delivery	IOF: Implementation Cost RE-AIM: Implementation	The cost of implementation, depends upon the costs of the BISC implementation techniques.	-	Administrative data					●	
**Effectiveness outcomes**	Secondary outcome	7-day point abstinence status		Self-reported abstinence from smoking for the past 7 days.	Quantitative data and qualitative data	-	Telephone callback			●	●	●

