The use of USPs is intended to mitigate observation bias and provide a valid, objective, and precise measurement^18,19^. We will employ three USP cases involving male current smokers with hypertension, type 2 diabetes, and cold, all requiring clinicians to provide BISC per national clinical practice guideline (Supplementary file Appendix C). Previously, our study developed, validated, and implemented 11 USP cases^20^ to evaluate the quality of PHC services, which contain a quality assessment checklist for the correct disposition of the physician in the desk design (Supplementary file Appendix D). These cases are reflective of the most prevalent conditions encountered in the PHC provider. The present study employed a standardized and well-established USP recruitment, training, and quality-control system based on the research team’s prior USP-based projects. Based on our previous experience, where a single USP can complete up to 72 visits per month, recruiting 20 USPs is sufficient to cover all 640 clinicians. In total, 20 USPs will be recruited across three regions, with approximately 6–7 USPs allocated to each city. All clinicians in the PSUs (a total of 640) will receive at least one USP visit. Each USP is scheduled to conduct a total of 32 visits. USP assignments to clinicians and clusters are performed using a random number table to ensure randomization and balanced coverage across clusters.

The sustainability of BISC delivery, defined as the likelihood of the intervention being maintained in practice, will be measured using the Program Sustainability Assessment Tool (PSAT)^21^. The sustainment of BISC delivery, or continued implementation over time, will be measured six months after the intervention. As USP visits are not suitable for long-term follow-up due to the risk of the standardized patients being recognized by clinicians, we will measure sustainment using the Provider Report of Sustainment Scale (PRESS)^22^ and semi-structured interviews to assess clinicians’ self-reported behavior and perceptions. The appropriateness of BISC delivery will be measured by Normalization Process Theory (NPT)-guided questionnaires (Supplementary file Appendix E)^23^, while its acceptability will be assessed through semi-structured interviews. Lastly, costs associated with the implementation strategies will be measured using administrative data.

Secondary aim: effectiveness outcomes

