The secondary aim of this study is to assess the effects of the BISC intervention on patient-level outcomes. These outcomes will be measured via a patient phone call survey at two distinct time points. At the end of the intervention, a phone call will be made to all patients who were identified as smokers and received the BISC intervention during the study period. This initial survey will assess their smoking status immediately following the intervention and confirm their receipt of the BISC components. A 6-month follow-up survey will then be conducted exclusively with patients who self-reported as smokers and received the BISC intervention. This survey will assess the long-term effectiveness of the intervention by measuring key indicators, including 7-day point abstinence status, daily cigarette consumption, and patient satisfaction with the BISC provided by the clinician. A summary of all outcome measures, their respective assessment methods, and time points is presented in Table 2.

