Qualitative data analysis from stakeholders will be de-identified and imported into Nvivo 11.0 for transcription, organization, coding, and content analysis. Our qualitative data analysis will use a mixed approach, combining both deductive and inductive methods, to identify established themes, patterns, and new discoveries^28,29^. For the first phase of the study, data from our scoping review^30^ and stakeholder consultations were analyzed deductively using the Consolidated Framework for Implementation Research (CFIR)^31^ to identify barriers and facilitators. For the second phase, data from semi-structured interviews will be analyzed inductively to find new themes. These data will also be analyzed using NPT to evaluate how the BISC intervention is integrated and sustained in practice. To ensure our coding is reliable, two team members will independently code each interview, and any differences will be resolved through discussion.

The systematic decision-making process^32^, guided by data from the factorial trial, will be integral to this procedure. We will leverage the estimated main effects to identify techniques that have a statistically significant positive impact. We will also examine interaction effects to glean insights into potential synergies or antagonisms between the techniques. The final optimization of implementation strategies will be achieved by integrating information from both main and interaction effects, along with a consideration of the predetermined constraints of the optimization objective. This approach ensures that the final selection of techniques is the most effective and efficient combination.

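### Endline coverage (Reach) is assigned to standardized-patient visits, all by scripted male smokers, although it is defined on patients attending primary care

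*Protocol article*

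**What the plan says.** All of this stands in the protocol article, mostly under Study variables.

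- Table 2 lists coverage of BISC delivery as a secondary outcome, labelled Penetration and Reach, and defines it as "Percentage of patients who received BISC as compared to the patients who attended to PHC". It is typed as a percentage and marked in periods II to V. Its acquisition entry names both USP visits and telephone callbacks and points to footnote b.
- Footnote b divides the two methods by period: "Data collection via telephone callbacks with patients in periods I and V; Data collection by USP visits in period IV". Footnote a identifies IV as endline and V as follow-up six months later.
- The Outcomes text describes "three USP cases involving male current smokers with hypertension, type 2 diabetes, and cold". Twenty USPs are recruited, and "Each USP is scheduled to conduct a total of 32 visits".
- Table 2 also marks telephone callbacks in II to V for the patient sociodemographic row ("Gender, age, primary diagnosis, etc").
- For the effectiveness outcomes, the endline contact is described as follows: "a phone call will be made to all patients who were identified as smokers and received the BISC intervention during the study period".
- Under Data analysis, "For continuous outcomes, GEE models with a Gaussian distribution and identity link function will be employed".

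**The concern.** The definition needs a denominator of people who attended. A USP visit samples none of them: the visitor is scripted, male and always a smoker. What such visits measure is whether a clinician delivers BISC to a smoker who presents. That is fidelity, which the primary outcomes already measure on the same visits.

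If footnote b is followed, the plan's only Reach outcome becomes at endline a second fidelity figure under another label. A reader would take it as the share of attending patients reached. Values from callbacks in other periods would come from a different population and a different instrument, so they would not belong in one series with it. If no general attendees are sampled at endline, the gap cannot be filled afterwards.

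**Working it through.** **Step 1. What the endline data would be.** 20 USPs × 32 visits = 640 visits, which equals 8 conditions × 80. Under footnote b these 640 visits are the endline source for coverage, and none is an attending patient.

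**Step 2. Definition against source.**

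| | Coverage as defined | USP visits in IV |
|---|---|---|
| Who is counted | All who attended | Scripted visitors |
| Sex | Any | Male |
| Smoking status | Any | Current smokers |
| Condition | Any | Hypertension, type 2 diabetes, cold |
| Construct | Reach | Fidelity |

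**Step 3. Size, as an illustration.** The plan states no coverage figure to reproduce. Let s be the smoker share of attendees, q the delivery rate in smokers and f the rate in non-smokers counted as covered. Then

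coverage C = s × q + (1 − s) × f, while USP visits return q.

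The two agree only if s = 1 or f = q.

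Inputs:
- q = 33.9% and 47.46%, the advice-to-quit rates under Sample size and power (33.9% × 1.40 = 47.46%). Using advice to stand for receipt of BISC, and reading 33.9% as a rate among smokers, are assumptions.
- s is not given. I borrow 20% and 27.7%, the adult smoking target for 2030 and the 2015 rate in the Introduction. These are not rates among attendees.
- f is not given. I use 0, 10% and 20%.

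Level at q = 33.9%:

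| s | f | C | USP value ÷ C |
|---|---|---|---|
| 20% | 0 | 0.20 × 33.9 = 6.78% | 5.0 |
| 27.7% | 0 | 0.277 × 33.9 = 9.39% | 3.6 |
| 20% | 10% | 6.78 + 8.00 = 14.78% | 2.3 |
| 27.7% | 10% | 9.39 + 7.23 = 16.62% | 2.0 |
| 20% | 20% | 6.78 + 16.00 = 22.78% | 1.5 |
| 27.7% | 20% | 9.39 + 14.46 = 23.85% | 1.4 |

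Outside that range of s, with f = 0, s = 15% gives 6.7 and s = 40% gives 2.5.

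**Step 4. Absolute difference between conditions.** If f is the same in both conditions, the true difference is s × (47.46 − 33.9) = s × 13.56 points: 2.71 points at s = 20% and 3.76 at s = 27.7%. USP visits would show 13.56 points, 5.0 and 3.6 times as much. If a technique also raises f, the true difference is larger and the factor smaller.

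**Step 5. Ratio between conditions.** With f = 0, s cancels: 47.46 ÷ 33.9 = 1.40 on either basis. With f = 5% in both conditions and s = 27.7%, C is 13.01% and 16.76%, a ratio of 1.29. The ratio is therefore preserved when non-smokers do not count, or when f moves in proportion to q, but not in general.

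**The case against.** **A usable endline source may already exist.** The coverage row names callbacks as well as USP visits, and the patient row marks callbacks in IV. Data analysis adjusts for and subgroups by patient smoking status, which cannot vary among USPs. A reader might infer that USP visits are the sole endline source and that the trial will hold no attendee data. The documents do not support that: footnote b does not say 'only', and the analysis text suggests callbacks that include non-smokers. What remains is that footnote b exists to split the methods by period and gives IV to USPs. The sentence on combining both methods names three other secondary outcomes, not coverage. The one endline call described in the text reaches smokers who received BISC, which is the numerator alone.

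**The footnote is visibly faulty.** It names period I, where the row has no mark, and gives no method for III. That is a wording slip. Reading I as II leaves IV with USPs. Nor is this a detail left to a fuller protocol: the article states both the definition and the source, and they do not fit.

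**The figures are soft.** This stands. The Introduction gives 33.9% as a share of patients, not of smokers. If it is already a rate among all attendees, multiplying by s discounts it twice. Core intervention lists asking about smoking as part of BISC, so f = 0 is the extreme case. The overstatement is also on the absolute scale: the identity link applies if coverage is analysed as a percentage, whereas one yes/no result per visit could go into a log-link model, where the distortion may vanish.

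**Two stronger readings are tempting.** One is that unchanged practice would show a spurious rise from baseline to endline and a fall at six months. That needs callbacks drawn from all attendees, whereas the six-month survey is described as limited to smokers who received BISC. It also needs contrasts over time, which Data analysis does not plan. The other is that inflated Reach would distort the choice of techniques. The decision step uses main and interaction effects, "along with a consideration of the predetermined constraints of the optimization objective", and does not name coverage as an input.

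**Conclusion.** The point holds as a conflict between an outcome's definition and its stated endline source. Coverage taken from USP visits in period IV is delivery to standardized smokers, not Reach, and should not be set beside callback values. The illustrative overstatement of its level is about 1.4 to 5 times, and of an absolute difference between conditions 3.6 to 5 times if delivery to non-smokers does not differ between conditions. Both rest on a borrowed smoker share, on a 33.9% rate read as applying to smokers, and on assumed handling of non-smokers. If coverage was meant among smokers alone, the scale gap goes, but the definition does not say so. Ratios between conditions may survive. The primary outcomes, for which USP visits are suitable, are unaffected. This is a secondary outcome that should be corrected before endline; confidence is medium because the full protocol may assign the callbacks differently.

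**What to change.** In footnote b, separate coverage from the fidelity items. Keep USP visits in IV for the fidelity items. For coverage, state that period IV uses the patient telephone callbacks that Table 2 already marks there, with all called attendees as the denominator, whether or not they received BISC. Correct the period I entry and name the method for III in the same edit.

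The cost is one footnote. If the endline calls were planned only for BISC recipients, some other attendees must be called as well.

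If that is not feasible, relabel the endline USP value as BISC delivery to standardized smokers, drop the Reach label for it, and do not report it in one series with callback values. This needs no new data but leaves the trial without a Reach measure at endline.
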